**Figure 1 figure1:**
[figure not shown]
Illustration of the training exercises used to train attentional control: (A) in this Neuropeak updating exercise, the task consisted of indicating whether the current symbol (eg, a star) matches (or does not match) the previously displayed symbol in 1-, 2-, or 3-back position. (B) In this Neuropeak inhibition exercise (incongruent trials), the task consisted of indicating the number of copies (eg, 5) of the digit displayed in the center of the screen (eg, 2). (C) In this general knowledge quiz game, the task consisted of indicating the number of the correct answer (eg, 4) to the question displayed in the upper part of the screen.

Inhibition training also involved 2 Stroop-like exercises with different sets of compound stimuli. Both sets were performed during each of the 12 training sessions. The first set comprised compound stimuli made from digits (1 to 6) and the second included compound stimuli made from letters (D, F, H, L, S, T). The 2 different sets were used to reduce the stimulus–response dependency of the improvement in performance on tasks, and hence facilitate transfer. Stimuli was displayed in the center of the screen (Figure 1B). In the first set, participants were asked to count the number of items in each trial while in the second set, they were asked to identify the largest letter. In each set, they were presented 3 types of stimuli: congruent (eg, 5 copies of the digit “5” or a large “H” formed from smaller Hs), neutral (eg, five copies of the symbol “*” or a large “H” formed from smaller “*”), and incongruent (eg, 5 copies of the digit “3” or a large “L” formed from smaller Hs). Each of the 2 sets comprised 7 blocks. The first block contained 20 congruent compound stimuli, the second block contained 60 neutral stimuli, and the third 60 incongruent compound stimuli. Incongruent items require inhibiting the smaller stimuli to determine the larger one. The congruent and incongruent blocks were then repeated twice in alternance. Participants were instructed to respond as fast as possible while maintaining high accuracy. Response keys were displayed on both sides of the touchscreen, and participants responded with their thumbs. Participants were instructed that there was no time limit but responses taking longer than 4 seconds were not recorded to avoid the impact of outliers. A response immediately triggered the following target in order to reduce the contribution of task preparation to performance.

For both inhibition and updating training, visual feedback was provided for each response by changing the color of the response button to green when correct or red when incorrect. Moreover, successive correct answers were combined with positive visual feedback (ie, good, great, amazing, unbelievable) and displayed in the center of the screen below the target. At the end of each training session, an individualized graphic representation depicted the participant’s average daily performance (ie, the mean of reaction time divided by 1, minus the proportion of errors) and plot progression from the beginning of training (Figure 2).

**Figure 2 figure2:**
[figure not shown]
Illustration of a graph showing the progress of a fictive participant from the inhibition training group through each session. The score is the IES (Inverse Efficiency Score).

The active control is a general knowledge quiz intervention run with E-Prime 3.0 software (Psychology Software Tools, Inc) on a laptop (Lenovo; Figure 1C). Previous studies have found that casual video games appear to be well suited as an active control condition [42,43], especially for computerized cognitive training where frequent responses are requested. Furthermore, a quiz game that does not require significant attentional control processes can appear to be a credible computerized cognitive training to the participants. An additional advantage of using a quiz game is that semantic knowledge and vocabulary are cognitive components that are unaffected by aging. As a result, semantic training was not expected to yield substantial cognitive benefits outside of the practiced task. Participants were presented with a series of 4-choice questions on 18 different topics (960 questions on food, science, geography, video games, history, sports, music, inventions, animals, movies and television series, art and literature, Canada, physics and space, monuments in the world, key historical dates, people and languages, herbs and spices, and fruit trees). The questions were adapted from OpenQuizzDB [44] or created by our research team. Each session included 2 blocks of 40 new questions. After an overall randomization of the entire pool of questions, they were displayed one by one in the same order for all participants, who had a maximum of 20 seconds to provide their response. Below each question, multiple answers (numbered 1, 2, 3, and 4) were displayed. Participants responded by pressing the corresponding number on a keypad. The selected questions were rated as medium difficulty on the OpenQuizzDB website. Positive feedback (ie, happy face emojis with the message “Bravo” or “Excellent, this is the right answer”) and a short explanation was provided following correct answers. Informative feedback (ie, “this is not the right answer”) and a short explanation was provided following incorrect answers, and displayed a second time at the end of the block.

To improve adherence, participants completed their training using individual tables, but in small groups of 6-10 individuals under the supervision of a trainer, who answered questions related to the task, helped manage technical issues, and encouraged completion of all exercises. All training sessions took place in the same room located at the CRIUGM. Five students were trained who rotated to ensure consistent supervision of training sessions.

### Baseline Characterization

At baseline, participants provided demographic information (age, sex, education), completed a Cognitive Reserve Proxy Questionnaire (CRQ) [45], Ischemic Index [46], and depression questionnaires (short version of Geriatric Depression Scale [GDS] for older adults [47] and Beck Depression Inventory II (BDI-II) for young adults). Cognition was measured with the Montreal Cognitive Assessment (MoCA) [48] and a French version of the Logical Memory Subtest from the Consortium for the Early Identification of Alzheimer’s Disease (CIMA-Q) [41] adapted from Wechsler Memory Scale [39]. Participants provided a saliva sample with the Oragene OG-500 collection kit at POST2 (V10). The sample was used to determine the single-nucleotide polymorphism rs4680 (Val^158^Met) of the *COMT* gene, the rs6265 (Val^66^Met) of the *BDNF* gene, and the rs7412 and rs429358 of the *APOE* gene.

An MRI examination was used to measure brain structure and function at the Functional Neuroimaging Unit of CRIUGM, using a Siemens Magnetom Prisma Fit 3 Tesla scanner (32-channel head coil). This will provide measures of baseline brain status, some which will be used as moderators and others as outcomes (see below for sequences used as outcomes). Sequences will be used to determine baseline intracranial volume, regional volumes (repetition time [TR]/echo time [TE] 2300/2.98 ms, Fa 9°, field of view [FOV] = 256 × 256, matrix 256 × 256, voxels 1 mm^3^, 192 slices), and volume of white matter lesions taken with the fluid attenuated inversion recovery sequence (TR/TE 9000/120 ms, Fa 90°, FOV 240 × 240, matrix 256 × 256, voxels 0.9 × 0.9 × 3 mm, 48 slices).

### Effect on the Trained Tasks

The improvements on the trained tasks will be reported using inverse efficiency scores (IESs) for each participant, which corresponds to the mean of the reaction time per session divided by the proportion of error minus one. These scores will be calculated for the 1-, 2-, and 3-back blocks separately for the updating training and separately for congruent and incongruent blocks for the inhibition training.

### Effect on Transfer Tasks

#### Transfer to Proximal Outcomes

An updating composite score and an inhibition composite score will be used as proximal and primary outcomes. The updating composite score will be computed by averaging the z-scores 

 from the keep track task and the running span task, where the calculation of 

 and "s" are based on the data from the PRE of each task. In the keep track task [49], participants were presented lists of 12 words from four different categories (eg, fruits, clothes, music, colors). The words were displayed one by one on a computer screen and participants were asked to report the last word belonging to each of the 4 categories. Participants updated their WM content each time they encountered a new word from the same category. The dependent variable is the proportion of words correctly recalled. In the running span task, participants were presented with lists of letters displayed one by one on a computer screen. The size of the lists varied randomly from n, where n is the participant’s letter span minus 1, to n + 6. Participants reported the n last letters in their correct order but were not informed of list’s length in advance. The dependent variable is the proportion of letters correctly recalled.

As described above for the updating composite score, the inhibition composite score will be computed by averaging z-scores 

 from the antisaccade task and the Victoria Stroop Test. In the antisaccade task [50], participants were asked to indicate their response with a key controlling the pointing direction of an arrow (up or down) presented in the right or left portion of a computer screen. Prior to the arrow presentation, a flashed cue will appear on the opposite side of the screen. The dependent variable is the proportion of correctly identified target arrow directions, despite the distracting cue. In the Victoria Stroop Test [51], participants were first asked to name colors using dots printed in color, noncolor words printed in color, and finally, the names of colors printed in different colors than its name. The dependent variable is the reading time for the incongruent colored words divided by the reading time for the dots printed in color. The directionality of the z-scores will be turned in the same direction as the antisaccade task (ie, higher is better).

#### Transfer to Complex WM

Performance on complex WM tasks will be measured using the alpha-span [52] and reading-span [53] tasks. In the alpha-span task, participants were asked to orally recall 5 series of words in alphabetical order rather than in the order of presentation. The words were read aloud by the assessor at a rate of 1 item per second; the size of the series corresponded to n minus 1. Prior to the alpha-span task, an individual’s n was determined as the longest sequence of words that could be repeated in the same order as presented. The dependent variable is the proportion of words recalled in the correct order. In the reading-span task, participants made yes/no semantic plausibility judgments on a series of 2-5 sentences. Following each series, participants were asked to recall orally the last word of each sentence. The dependent variables are the proportion of correct words recalled.

#### Transfer to Complex WM in Virtual Reality

An immersive virtual reality dual task was used to reflect transfer to situations that require closer to real-life cognition [10]. The task was presented with Virtools 5 (EDS Technologies) on a Dell Precision T3600 PC (Inter Xeon CPU ES-1620 0 3.60 GHz, 10-GB RAM processor, and NVIDIA GeForce GTX 600) using an HMD nVisor ST50 headset with stereoscopic vision (1280 × 1024 full color with 50° diagonal field-of-view). During this task, participants were sitting in a car as a passenger and asked to detect road signs (by pressing the left mouse button) to guide the driver to the cities “Chauminont” or “Montformeil.” Forty road signs were presented, and half were targets. At the same time, participants memorized and recalled a series of 12 words aloud, which were presented orally by the driver. The dependent variable is a dual-task score computed by averaging z-scores on the memory and detection (accuracy and reaction time) tasks.

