### Interventions

The 2 experimental training conditions (inhibition and updating) were provided by the Neuropeak web platform ([name] et al, unpublished data) using a Samsung Galaxy Tab 2 (Android version 4.2.2).

The updating training involved 2 N-back-type exercises (1-2- and 3-back) with different sets of stimuli. Both sets were performed during each of the 12 training sessions. The first set comprised stimuli made from digits (1 to 9) and the second comprised symbols (moon, planet, star, dog, bird, snake). The stimuli were displayed on the center of the screen, one by one, at the rate of 4 seconds per item (Figure 1A). In both sets, participants were asked to indicate whether each item matches the one presented in the *n* position previously (eg, 3-6-3-9-9 wherein the second “3” is the only match in a 2-back block). Each round comprised 8 blocks grouped by N-back level and performed in the following order: 1-back (2 × 11 trials), 2-back (3 × 12 trials), and 3-back (3 × 13 trials). Each of the 8 blocks were set to include 40% “match” responses. Nonetheless, participants were able to reach the 3-back level only if their accuracy was equal or above 75% at the 2-back level. If they were below this percentage, they finished the round with a 1-back block instead. Participants were instructed to respond as fast as possible. “Match” and “Mismatch” buttons were permanently displayed on the right side of the screen and participants were required to answer with their right thumb.

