#### Analysis of Behavioral and Brain Outcomes

We will use a modified intention-to-treat analysis of behavioral outcomes to minimize attrition-related bias, so that all participants who have completed at least one postbaseline assessment will be analyzed. The effect of training programs on the behavioral outcomes will be analyzed with linear mixed-effects models (LMMs) as this analysis makes it possible to compare performance growth between groups and is resistant to missing values. Training improvements will be tested using IES as the dependent variable with 2 separate analyses using *session* (12 levels: session 1 to session 12) *× condition* (3 levels: IES 1-back/IES 2-back/IES 3-back) for the updating training and *session* (12 levels: session 1 to session 12) *× condition* (2 levels: IES Congruent/IES Incongruent) for inhibition training. When significant interaction effects are found, pairwise comparisons will be computed within each training group (comparing performances at sessions 6 and 12 to session 1) and between training conditions at sessions 6 and 12.

Efficacy of training to improve proximal task performances will be tested at 2 separate *time* (three levels: PRE/POST2/POST4) × *training* (3 levels: inhibition/updating/general knowledge) LMMs, using inhibition and updating composite scores as dependent variables. When significant interaction effects are found, pairwise comparisons will be computed within each training group (comparing performances at POST2 and POST4 to PRE) and between training groups (comparing performances for the inhibition and updating condition to general knowledge condition) at POST2 and POST4. To reduce the statistical power cost due to multiple testing corrections and as we have a priori hypotheses, we will also conduct LMM analyses in the absence of interaction to make a direct comparison between the performances of the general knowledge training group (control active) and the updating or inhibition training groups separately.

Efficacy of training to improve complex WM will be tested in the same way with separate time-varying LMMs (5 levels: PRE/POST1/POST2/POST3/POST4) × *training* (3 levels: inhibition/updating/general knowledge) for each task (ie, reading span, alpha span, and VR composite score).

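### The virtual-reality score mixes reaction time with memory and accuracy, and only the trained arms have a stated speed instruction, so a trained-versus-control difference cannot be attributed to working memory rather than response speed

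*Protocol article*

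**What the plan says.** **The outcome.** In the section Transfer to Complex WM in Virtual Reality, participants memorise words while they are "asked to detect road signs (by pressing the left mouse button"). The score is defined as follows: "The dependent variable is a dual-task score computed by averaging z-scores on the memory and detection (accuracy and reaction time) tasks". In Analysis of Behavioral and Brain Outcomes, the five-occasion time × training mixed models for complex working memory are specified "for each task (ie, reading span, alpha span, and VR composite score"). The article names no model for the separate VR components. The Objectives describe the VR tasks as reflecting working memory in real life, and the Discussion presents them as the study's innovative measure of everyday transfer.

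**The trained arms.** In the Interventions section, the updating arm is given a speed instruction: "Participants were instructed to respond as fast as possible". The inhibition arm has a similar one: "Participants were instructed to respond as fast as possible while maintaining high accuracy". After each session both arms see a progress graph of an efficiency score, described as "the mean of reaction time divided by 1, minus the proportion of errors".

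**The control arm.** Quiz questions were shown one at a time to participants "who had a maximum of 20 seconds to provide their response". The response mode is also given: "Participants responded by pressing the corresponding number on a keypad". Feedback concerns correctness. No speed instruction is stated.

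**The limitations.** The Discussion warns that the quiz may itself stimulate working memory and so shrink the contrast with control. It does not mention the difference in speed demands.

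**The concern.** One of the three inputs to the VR score is a latency, and the arms differ by design in how much they practise answering quickly. If twelve sessions of speeded practice make participants respond faster in general, the reaction-time part of the composite improves in both trained arms relative to the quiz arm, even when memory and detection accuracy do not change. The composite alone cannot show which part moved.

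The other transfer scores are less exposed. Keep track, running span, antisaccade, alpha span and reading span are scored as proportions correct. The Victoria Stroop score divides the incongruent time by the dot-naming time, which takes out much of general speed. The VR score is the only transfer score with a latency that is not referenced to a control condition, and it carries the real-life claim.

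At stake is the interpretation of Objective 2(iii). A speed gain shared by both programs could be read as everyday working-memory transfer from both. This bias runs in the opposite direction to the one that the Discussion warns about.

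**Working it through.** The article gives no effect size, correlation or weighting for the VR score, so there is no stated figure to reproduce. The check has two parts: the practice contrast from the text, and an illustration of size under stated assumptions.

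**1. Practice contrast (Interventions section)**

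Responses per session, assuming one round of each set per session and repeated blocks of the same length:
- Updating, if the 3-back level is reached: 2 × (2×11 + 3×12 + 3×13) = 2 × 97 = 194, under a speed instruction.
- Inhibition: 2 × (20 + 60 + 60 + 2×(20 + 60)) = 2 × 300 = 600, under a speed instruction.
- Quiz: 2 × 40 = 80, up to 20 seconds each, no stated speed instruction.

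All three arms press buttons or keys. The contrast lies in speeded responding with reaction-time feedback.

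**2. Effect of a speed-only gain on the composite**

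Inputs:
- n = 27 per arm and α = .05, from Sample Size; the test is taken as two-sided.
- Assumed: reaction time is coded so that higher is better. The VR section does not state the reversal.
- Assumed: gain over control g = 0.5 SD in reaction time, none in memory or accuracy.
- Assumed: common inter-component correlation ρ from 0 to 0.4.
- Weights: the score is described by two tasks, with accuracy and reaction time bracketed under detection, and Table 1 lists two components (verbal memory, visual detection). Weights of 1/2, 1/4, 1/4 are therefore the more natural reading. Equal thirds is the alternative.

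Formulas:
- Composite variance: V = Σw² + ρ(1 − Σw²)
- Standardised composite effect: d = w_RT × g / √V
- Rejection probability: two-sided noncentral t, 52 degrees of freedom, noncentrality d√(27/2)

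One-quarter weight (Σw² = 0.375), g = 0.5, shift 0.25 × 0.5 = 0.125:
- ρ = 0: V = 0.375, d = 0.125/0.612 = 0.204, rejection 11.4%
- ρ = 0.4: V = 0.375 + 0.4×0.625 = 0.625, d = 0.125/0.791 = 0.158, rejection 8.8%

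Equal weights (Σw² = 0.333), g = 0.5, shift 0.167:
- ρ = 0: V = 0.333, d = 0.167/0.577 = 0.289, rejection 18.0%
- ρ = 0.4: V = 0.333 + 0.4×0.667 = 0.600, d = 0.167/0.775 = 0.215, rejection 12.1%

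Sensitivity to the size of the gain:

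| Speed-only gain | One-quarter weight | Equal weights |
|---|---|---|
| 0.3 SD | 6–7% | 8–10% |
| 0.5 SD | 9–11% | 12–18% |
| 1.0 SD | 21–31% | 34–55% |

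Without a reaction-time component the shift is 0 and the rejection rate is the nominal 5%. These are single-occasion two-group comparisons. They show the order of magnitude and are not the error rate of the planned five-occasion mixed model.

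**The case against.** The strongest reply is that reaction time belongs in a dual-task score. Slower detection while words are held in memory is a cost of dividing attention, and attentional control is what the programs train, so faster detection under load may be the intended transfer. This stands. A reader might infer that any VR gain would be mere button-pressing speed, but nothing in the article shows that detection latency is purely motor. The response modes also differ: thumbs on a touchscreen in the trained arms, a keypad in the quiz, a mouse button in VR. Carry-over of speed is plausible but is not shown.

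It can also be said that the absence of a speed instruction in the quiz arm is silence in a condensed article, and that a full protocol or analysis plan may provide for component reporting. Both are fair. However, the 20-second limit and the correctness-only feedback are stated, and they contrast with the stated instruction and feedback in the trained arms.

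The size should not be overread. Rejection rates of 34–55% need a 1.0 SD gain on an untrained latency together with equal weights, and the article supports neither.

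Finally, the VR score is not a primary outcome; the updating and inhibition composites are. A speed-only effect would appear as an isolated VR finding beside alpha span and reading span, which would give an attentive reader some warning. These points limit the seriousness, but they do not make the composite able to separate the two explanations.

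**Conclusion.** The point holds as a limit on attribution. With the composite as the only named VR variable and unequal practice in speeded responding, a trained-versus-control difference cannot be assigned to working memory rather than response speed. It does not follow that a VR gain must be an artefact.

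The size is modest: on the more natural weighting, roughly double the nominal 5% for a 0.5 SD speed-only gain, and little above 5% for 0.3 SD. The gain, the correlations, the weights and the direction of coding are all assumptions. The comparison of inhibition with updating, which the Discussion names as a main strength, is much less affected because both arms are speeded. The matter is worth correcting because the real-life claim rests on this score and the remedy uses data already collected.

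**What to change.** Keep the composite as stated. Dropping reaction time from it would change a stated outcome after data collection ended (April 2019, with analysis begun in June 2020), and it would let slow, careful responding count as gain. Instead:

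1. Add time × training mixed models, on the same five occasions, for VR memory, detection accuracy and detection reaction time, the last labelled as response speed.
2. Document and date these models as an addition, and state the component weights and the direction of the reaction-time z-score.
3. State that a trained-versus-control effect on the composite will be called working-memory transfer only if memory or detection accuracy also supports it and it is not carried by reaction time alone.
4. Add the difference in speed demands between the arms to the limitations.

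The cost is three additional models on existing data and a somewhat more conservative VR conclusion. A genuine attentional benefit that appears only in reaction time would be reported as response speed.
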